### Sample size

According to our previous experience [26], we estimated that around 20% of patients in the control group will present positive cultures of the catheter hubs. A reduction of this figure to 5% in the taurolidine-citrate-heparin group would be clinically relevant. To detect a 15% difference between groups with a power of 80%, it would be necessary to include 135 patients in the study. Considering the possibility of a loss of 10% of cases, the final sample should be 150 patients.

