### Statistical analysis

The analysis of the data will be carried out during the last 6 months of the project when all fieldwork has been completed. The database will then be analysed using the stepwise logistic regression model of the R software (R v. 3.2.5). The analyses will be made by intention-to-treat (all patients randomised who have a primary endpoint available). To handle missing data multiple imputation will be done under the missing at random assumption.

For the analysis of the primary endpoint, the frequency of colonisation of the CVC hubs in both treatment groups will be compared. For the analysis of the secondary endpoints, the frequency of CRBSI will be compared between the two groups, as well as the need for CVC removal for any cause and overall case-fatality rate (30 days). Exploratory subgroup analyses will be conducted by underlying haematological condition (leukaemia, autologous HSCT, and allogeneic HSCT) and by centre. Due to the fact that a patient could have been included twice, the potential impact of independence violation will be assessed repeating the main analysis using patient as a cluster.

The statistical analysis will be carried out using a Student’s *t* test and a chi-square test. A multivariate analysis will be performed to verify the absence of confusion by other variables. In addition, free time of colonisation of the catheter and BSI will be analysed using Kaplan-Meier curves, and they will be compared between both groups by means of the log-rank test (Mantel-Cox test). A value of *p* = 0.05 will be considered statistically significant.

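### 135 evaluable patients fall somewhat short of the stated 80% power for 20% versus 5%; under a two-sided chi-square reading about 142 to 152 are needed

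*Protocol article*

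**What the plan says.** The Sample size section of the protocol article assumes that "around 20% of patients in the control group will present positive cultures of the catheter hubs" and adds: "A reduction of this figure to 5% in the taurolidine-citrate-heparin group would be clinically relevant". From these rates it concludes: "To detect a 15% difference between groups with a power of 80%, it would be necessary to include 135 patients in the study". It then allows for loss: "Considering the possibility of a loss of 10% of cases, the final sample should be 150 patients".

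The other inputs stand elsewhere. Study design gives a parallel superiority trial with 1:1 allocation. Statistical analysis says that the frequency of hub colonisation will be compared between the groups, names R as the software and a Student's *t* "test and a chi-square test" as the tests, and sets the level: "A value of *p* = 0.05 will be considered statistically significant". The article does not say whether the test is one- or two-sided, and it names no sample-size formula.

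**The concern.** A sample-size statement can be checked when the two rates, the allocation, the level, the power and the test are known. All are given here except sidedness. A chi-square test on a 2×2 table is non-directional and the article announces no one-sided test, so two-sided 5% is the natural reading. On that reading the printed number and the printed power do not match, and the number is on the low side.

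This is the article's only power statement for the primary endpoint. If the trial ends without a significant difference, readers will judge the result against 80% power, which the design does not quite have at the evaluable number it states. Because 150 is built on 135, the shortfall carries through to the recruitment target.

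**Working it through.** **Inputs.** p1 = 0.20, p2 = 0.05, difference 0.15 and power 80% (z = 0.8416), from Sample size. Allocation 1:1, from Study design. Level 0.05 and chi-square test, from Statistical analysis. Two-sided (z = 1.96) is assumed. The mean rate is (0.20 + 0.05)/2 = 0.125.

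**Loss step.** 135/0.9 = 150. This reproduces the plan's final figure.

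**Evaluable patients for 80% power, two-sided.**

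- Pooled variance (the usual chi-square formula): n per arm = [1.96·√(2·0.125·0.875) + 0.8416·√(0.20·0.80 + 0.05·0.95)]² / 0.15² = (0.9167 + 0.3834)²/0.0225 = 75.1, so 76 per arm, **152** in total.
- Unpooled variance: n = (1.96 + 0.8416)²·(0.16 + 0.0475)/0.0225 = 72.4, so 73 per arm, **146**.
- Arcsine: h = 2·arcsin√0.20 − 2·arcsin√0.05 = 0.4763; n = 2·(2.8016)²/h² = 69.2, so 70 per arm, **140** (138.4 before rounding).
- Pooled with continuity correction: n = (75.1/4)·[1 + √(1 + 4/(75.1·0.15))]² = 87.9, so 88 per arm, **176**.
- Exact power of the uncorrected chi-square, by summing binomial probabilities over all tables with p < 0.05: 79.8% at 70 per arm and 80.4% at 71 per arm, so **142**.

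None of these returns 135, and each lies above it.

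**Power at 135 (67.5 per arm in the formulas; 67/68 by enumeration).**

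| Method, two-sided 5% | Power at 135 |
|---|---|
| Pooled: z = (0.15·√67.5 − 0.9167)/0.4555 = 0.693 | 75.6% |
| Unpooled: z = 0.15·√(67.5/0.2075) − 1.96 = 0.745 | 77.2% |
| Arcsine: z = 0.4763·√(67.5/2) − 1.96 = 0.807 | 79.0% |
| Exact, uncorrected chi-square | 78.3% or 78.5%, depending on which arm has 68 |
| Exact, Fisher | 76.7% or 71.1% |
| Exact, continuity-corrected chi-square | 68.9% or 67.5% |

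**Power if all 150 were evaluable (75 per arm).** 79.9% by the pooled formula; 82.7% by exact calculation for the uncorrected chi-square; 76.0% with the continuity correction.

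**Recruitment that a 10% loss would imply.** 146/0.9 = 162.2, so 163; 152/0.9 = 168.9, so 169. The plan has 150.

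**One-sided 5%, for comparison.** The pooled formula gives 120, the continuity-corrected formula 144, and an exact Fisher test about 134.

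**Approximations that fit poorly here.** A score-type formula on the log odds ratio gives about 118 two-sided. It is meant for small effects, and the log odds ratio here is ln 4.75 = 1.56. Even at 128 patients, which is more than 118, the exact power of the uncorrected chi-square is only 75.9%. A log odds ratio formula with the variance under the alternative errs the other way, at 178.

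**The case against.** The strongest reply is that the gap is small and depends on the method. The article fixes no formula. By arcsine the need is 138.4 before rounding, and power at 135 is 79.0%. By exact calculation for the uncorrected chi-square it is 78.3-78.5%. Both are within 2 points of 80%, and the control rate is itself only approximate. The 75.6% is a large-sample figure, with only about 3 events expected in the 5% arm (0.05 × 68 = 3.4). An unpooled z test enumerated at 67/68 even reaches 80.1% (79.5% at 68/68). This stands as a limit on the size of the point. It does not rescue 135: the unpooled z test is not the chi-square test that the article names, and every uncorrected chi-square calculation shown stays below 80%.

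A second reply is that sidedness is open, and a one-sided exact Fisher test needs about 134. The article names neither a one-sided test nor Fisher's test, so this would replace the stated analysis with another. A condensed article may leave formula and sidedness to a fuller document. Their absence is not the complaint; the mismatch between two printed figures is.

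Three stronger readings are tempting but not supported. A reader might infer that 80% is reached only at about 150 evaluable patients; that holds for the pooled approximation, whereas exact calculation passes 80% at 142. A reader might infer that 135 arose by taking 10% off a correct 150; the article does not show this, and 135/0.9 = 150 is right as printed. Nor does it mean anything that 135 is odd: it is what remains of 150 after loss, and 150 splits evenly. Finally, a reader might take the power to be about 68%; the article does not say that the continuity correction will be used, so that figure is a risk from a software default and not the planned power.

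**Conclusion.** The point holds in moderate form. With 20% versus 5%, 1:1 allocation and a two-sided 5% chi-square test, 135 evaluable patients do not give 80% power. The need is 146-152 by the standard formulas and 140-142 by the least demanding of the usual methods. The stated number is therefore low by about 5 to 17 patients (140 − 135 to 152 − 135), and power is overstated by about 1 to 4 points for an uncorrected analysis. If the continuity correction were applied, the overstatement would be about 11 to 12 points.

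The conclusion rests on two assumptions: a two-sided test, which the article implies but does not state, and the article's own rates. It is not a claim that the figure fails under every conceivable test and sidedness, nor that the trial is badly underpowered.

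**What to change.** Keep 150 randomised and replace the power sentence in Sample size with one that names its method, for example:

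> 135 evaluable patients give about 76% power (two-sided 5%, pooled normal approximation; about 78% by exact calculation for the uncorrected chi-square test) for 20% versus 5%; 80% power needs about 142 to 152 evaluable patients, depending on the method.

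In Statistical analysis, specify that the primary chi-square test is two-sided and without continuity correction, so that a software default does not lower the power further.

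If the sponsor did use another method or a one-sided test to obtain 135, the alternative is to state it and justify it.

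The cost is one or two sentences and a slightly less favourable stated power. No extra patients and no change to the planned comparison are required.

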### Statistical analysis

The analysis of the data will be carried out during the last 6 months of the project when all fieldwork has been completed. The database will then be analysed using the stepwise logistic regression model of the R software (R v. 3.2.5). The analyses will be made by intention-to-treat (all patients randomised who have a primary endpoint available). To handle missing data multiple imputation will be done under the missing at random assumption.

For the analysis of the primary endpoint, the frequency of colonisation of the CVC hubs in both treatment groups will be compared. For the analysis of the secondary endpoints, the frequency of CRBSI will be compared between the two groups, as well as the need for CVC removal for any cause and overall case-fatality rate (30 days). Exploratory subgroup analyses will be conducted by underlying haematological condition (leukaemia, autologous HSCT, and allogeneic HSCT) and by centre. Due to the fact that a patient could have been included twice, the potential impact of independence violation will be assessed repeating the main analysis using patient as a cluster.

The statistical analysis will be carried out using a Student’s *t* test and a chi-square test. A multivariate analysis will be performed to verify the absence of confusion by other variables. In addition, free time of colonisation of the catheter and BSI will be analysed using Kaplan-Meier curves, and they will be compared between both groups by means of the log-rank test (Mantel-Cox test). A value of *p* = 0.05 will be considered statistically significant.

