### Randomisation

In this randomised, double-blinded study, neither the patient nor any of the health staff will know which product is assigned to each patient.

A unique list of coded numbers containing the randomised solutions will be generated in the Clinical Research Unit. The randomisation will be performed in each block and stratified. The stratum will contain three groups: patients with leukaemia, patients undergoing an autologous transplantation, and patients undergoing an allogeneic transplantation. The random number generator of SAS version 9.2 will generate the three lists. Once generated, the list will be kept in the pharmacy file, in the pharmacy department of ICO Hospitalet with restricted access to the blinded personnel involved in the trial. When a patient from any of the two participating centres meets the inclusion criteria and signs the informed consent, an email with the recruitment sheet of the patient will be sent to the pharmacy department of ICO Hospitalet, where the randomisation will take place, by the investigator from the pharmacy department in charge of the study. The assignment will be made sequentially, and each patient will be assigned a randomisation number.

The taurolidine-citrate-heparin and the heparin-placebo solutions will be prepared in each pharmacy department, and they will be dispensed in 2.5-mL syringes identified with the name of the drug, defined as heparin/taurolidine-citrate, to maintain the blinding. Citrate is an anticoagulant substance without antimicrobial activity, which accompanies taurolidine as an antiaggregant agent. Both lock solutions are colourless and odourless, which makes further masking unnecessary. The blind will be open before the statistical analysis, but only when the trial has concluded and the definitive data will be registered in the database. Only in cases with suspected serious adverse events will the blinding be open.

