### Data collection

The following data will be collected: sex, age, type of underlying disease, other comorbidities, date of hospital admission, HSCT, type and date of HSCT, immunosuppressive therapy, concomitant medication, duration of neutropenia, type of CVC, days from CVC insertion to inclusion in the study, use of prophylactic antibiotics or antifungal agents, systemic antibiotic therapy, number of catheter locks per episode, results of the cultures of the hubs and CVC insertion site, any episodes of infection, episodes of CRBSI, the need for CVC removal and reason, development of complications, adverse reactions, overall case-fatality rate, CRBSI attributable case-fatality rate, and date of discharge.

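### The primary analysis is left ambiguous between stepwise logistic regression and a chi-square test, and about 17 expected events cannot support data-driven covariate selection

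*Protocol article*

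**What the plan says.** All of the following is in the protocol article.

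- Statistical analysis, first method named: "The database will then be analysed using the stepwise logistic regression model of the R software". No candidate covariates, no selection rule and no forced terms are given.
- Same section, primary endpoint: "the frequency of colonisation of the CVC hubs in both treatment groups will be compared".
- Same section, tests: a Student's t "test and a chi-square test", with one threshold ("0.05 will be considered statistically significant").
- Same section, purpose of the adjusted model: "A multivariate analysis will be performed to verify the absence of confusion by other variables".
- Same section: colonisation-free time is also compared by a log-rank test. The main analysis is to be repeated with patient as a cluster, but the section never identifies the main analysis.
- Sample size: "around 20% of patients in the control group will present positive cultures of the catheter hubs", with 5% as the target in the taurolidine arm, 80% power, 135 patients, and 150 after 10% loss.
- Randomisation: stratified in three groups (leukaemia, autologous transplantation, allogeneic transplantation).
- Data collection: the recorded items include "number of catheter locks per episode, results of the cultures of the hubs and CVC insertion site, any episodes of infection".
- Follow-up criteria and participant timeline: a positive hub culture ends the intervention.

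**The concern.** Three features combine.

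1. More than one procedure could be presented as the primary result, and they need not agree.
2. One of them selects covariates from the outcome data. Randomisation already protects the treatment contrast from confounding, so the selection has nothing to repair. The usual confidence interval and p-value take no account of it, and with few events it tends to push the odds ratio away from 1.
3. The text sets no limits on the selection. Treatment itself could be dropped, the stratification factor could be dropped, and variables measured after randomisation are not ruled out. The number of locks is the clearest example: colonisation stops the locks, so a low count is partly a consequence of the primary endpoint.

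At stake is whether the trial's main p-value and effect size come from a rule fixed in advance.

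**Working it through.** **Sample size as stated.** 135/0.9 = 150 reproduces the inflation for loss. The 135 itself is not reproduced by rounded standard formulas. The two-sided pooled formula gives per arm [1.960·√(2·0.125·0.875) + 0.842·√(0.20·0.80 + 0.05·0.95)]²/0.15² = 75.1, so 76, or 152 in total. The unpooled form gives 146 and the arcsine form 140. Sidedness is not stated; the one-sided versions give 120, 116 and 110. This does not alter the point, as the event counts show.

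**Expected events** = (N/2)·(0.20 + 0.05).
- N = 135: 67.5·0.25 = 16.9 (13.5 control, 3.4 taurolidine).
- N = 150: 75·0.25 = 18.75.
- N = 152: 76·0.25 = 19.0.

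**What these events can support.** Treatment plus a three-level stratum uses 1 + 2 = 3 parameters. That is 16.9/3 = 5.6 events per parameter at N = 135, and 18.75/3 = 6.3 at N = 150. At 10 events per parameter the trial supports 1.7 to 1.9 parameters; at 5 it supports 3.4 to 3.8. Treatment and stratum already use most or all of this.

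**Effect of stepwise selection, by simulation.** The protocol gives no candidate list, so the number of candidates is an assumption and a range is shown. Candidates are pure-noise baseline covariates, with about 68 patients per arm. The alternative is 20% vs 5%, with true log odds ratio ln[(0.05/0.95)/(0.20/0.80)] = ln 0.2105 = −1.56.

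| Noise candidates | Runs | Type I error, stepwise vs chi-square | Power, stepwise vs chi-square | Median log-OR, stepwise vs unadjusted |
|---|---|---|---|---|
| 6 | 2,000 | 5.3% vs 5.1% | – | −1.65 vs −1.61 |
| 10 | 600 | 5.2–5.8% vs 5.0% | 74% vs 78% | −1.71 vs −1.62 |
| 10, treatment not forced in | 400 | 6.0% vs 4.5% | 75.5% vs 81.5% | – |
| 15 | 2,000 | 6.3% vs 5.1% | – | – |
| 15 | about 600 | – | – | −1.81 vs −1.62 |

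With 10 candidates the median odds ratio moves from exp(−1.62) = 0.198 to exp(−1.71) = 0.181. The Monte Carlo standard error of a 5.8% rejection rate at 600 runs is √(0.058·0.942/600) = 1.0 point, so no type I inflation is demonstrated in that row. A further set of 1,000 runs (10 candidates, treatment forced in, assumed mean neutropenia of 14 days) gave power of 80% for chi-square, 80% for log-rank and 73% for stepwise. Chi-square and stepwise reached opposite verdicts in 10% of those trials.

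**If treatment is not forced in and consequences of the outcome are candidates.** Two were added to the 10 noise covariates, both assumed: a binary event with probability 60% if colonised and 15% otherwise, and a lock count with mean 3 if colonised and 5 otherwise. In 400 runs, type I error was 9.8% vs 5.8% for chi-square, and power 65% vs 80%. Treatment was dropped in 15% of runs under the alternative. The median odds ratio when it was kept was 0.11, against a true 0.21. With noise covariates only, treatment was dropped in about 4% of runs under the alternative.

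**The case against.** The strongest reply is that the section can be read sensibly. The primary endpoint is described as a comparison of frequencies, a chi-square test is named, the sample size is built on two proportions, the multivariate model is described as a check, and the log-rank analysis is introduced as an addition. Candidate covariates and selection rules are normally left to the analysis plan. Much of this stands: chi-square as the main test is a fair reading, and the missing candidate list is no fault in itself. It does not remove the problem, because the stepwise sentence is current text, comes first and applies to the whole database, and nothing ranks it below the chi-square test.

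Four stronger readings are tempting, and the document does not support them.

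- A reader might infer that the model's variable list contains consequences of treatment and outcome. The Data collection section lists what is recorded, including the hub cultures that are themselves the endpoint, and nowhere calls these items predictors. The text only fails to exclude them.
- A reader might infer that the trial's estimate and p-value are invalid. Stepwise selection does not touch the chi-square p-value, so the harm is conditional on the stepwise model being made primary.
- A reader might infer a materially inflated false-positive rate. With noise baseline candidates the excess is about 1 to 1.5 points or less in the table, and mostly within simulation error.
- A reader might see a fault in "The blind will be open before the statistical analysis". That sentence goes on to require that the trial has ended and the final data are registered, which is ordinary practice.

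**Conclusion.** The concern holds as an ambiguity about the primary analysis, aggravated by a poorly chosen stated method. The event count (16.9 at N = 135, 18.75 at N = 150) follows from the protocol's own rates and is secure.

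If the stepwise model supplied the primary result and only baseline variables were candidates, the harm would be modest. With 10 assumed candidates the loss is about 4 points of power (74% vs 78%), or 6 to 7 points in the other two simulations. The odds ratio is somewhat exaggerated (0.181 vs 0.198), and uncertainty slightly understated. The harm would be larger if post-randomisation variables entered, but those figures rest on assumed variables that the protocol does not name as covariates.

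This is a should-fix: it bears on the primary endpoint, but a sound test is already named and only its status is unclear.

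**What to change.** In the Statistical analysis section, before the blind is opened:

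1. Name one primary analysis: the between-arm comparison of hub colonisation. The chi-square test already named is acceptable. A version stratified by, or adjusted for, the three-level randomisation stratum is preferable (for example Cochran-Mantel-Haenszel).
2. Report a risk difference or odds ratio with its 95% CI.
3. Delete stepwise selection and the stated aim of ruling out confounding.
4. Label the log-rank test and any multivariable model as supportive.
5. Limit any adjusted model to one or two prespecified baseline covariates, with treatment always retained and no variable measured after randomisation.
6. State that the repeat analysis clustered by patient refers to this primary analysis.

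The cost is wording only, with no change to conduct, data or sample size. Stratum adjustment leaves 5.6 to 6.3 events per parameter in a logistic model, which is why the stratified test or the plain chi-square test remains a reasonable choice. What is given up is the predictor search as a main result; it can still be reported if labelled exploratory.

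### Randomisation is stratified by disease and transplant group, but the named chi-square and log-rank tests are not; if the strata differ in colonisation risk, these tests are conservative and some efficiency is lost

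*Protocol article*

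**What the plan says.** Under Randomisation, the protocol article states: "The randomisation will be performed in each block and stratified". It then names the strata: "The stratum will contain three groups: patients with leukaemia, patients undergoing an autologous transplantation, and patients undergoing an allogeneic transplantation". Three separate lists are generated.

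Under Statistical analysis:

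- Primary endpoint: "For the analysis of the primary endpoint, the frequency of colonisation of the CVC hubs in both treatment groups will be compared". No stratum is mentioned.
- Tests, listed for the analysis as a whole: a Student's t "test and a chi-square test".
- Time free of colonisation and of bloodstream infection: Kaplan-Meier curves, and "they will be compared between both groups by means of the log-rank test (Mantel-Cox test").
- Models: "The database will then be analysed using the stepwise logistic regression model of the R software (R v. 3.2.5"), and further on "A multivariate analysis will be performed to verify the absence of confusion by other variables".
- The only analysis that uses the three groups by name: "Exploratory subgroup analyses will be conducted by underlying haematological condition (leukaemia, autologous HSCT, and allogeneic HSCT) and by centre".

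**The concern.** Blocking within strata balances the arms on the stratum. If colonisation risk differs between strata, this balance makes the estimated treatment difference less variable than it would be under simple randomisation. A test that ignores the strata does not take credit for this. It still counts the between-stratum variation as error, so its standard error is larger than the design warrants and its true type I error falls below the nominal 5%. The same reasoning applies to the log-rank test.

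What is at stake is efficiency: a somewhat wide standard error and, at the planned effect, up to a few points of power that a stratified test would add without further patients.

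**Working it through.** **Inputs from the protocol article.** Control risk 20%, taurolidine risk 5%, 80% power, 135 patients before loss and 150 after 10% loss (Sample size); 1:1 allocation (Study design); significance at 0.05 (Statistical analysis), taken here as two-sided; three strata (Randomisation).

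**The plan's own figure.** The loss step reproduces: 135 / 0.9 = 150. The 135 does not follow from the usual two-sided formula for two proportions:

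n per arm = [1.96 × √(2 × 0.125 × 0.875) + 0.8416 × √(0.20 × 0.80 + 0.05 × 0.95)]² / 0.15² = (0.917 + 0.383)² / 0.0225 ≈ 75.1, so 76 per arm and 152 in total.

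By this formula power is 75.6% at 135 and 79.9% at 150. That is a separate matter. It is relevant here only because the planning calculation compares two proportions with no strata.

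**Assumptions, since the documents give no stratum sizes or rates.** Strata of 60, 42 and 34 patients (136 in all, 68 per arm), allocated 1:1 within each; the same odds ratio in every stratum; three sets of control risks with a pooled value of about 20%. For 6/20/45%: (60 × 0.06 + 42 × 0.20 + 34 × 0.45) / 136 = 27.3 / 136 = 20.1%. For 12/20/34%: 27.16 / 136 = 20.0%. In each set the odds ratio is chosen so that the pooled taurolidine risk is 5%.

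**Simulation.** Pearson chi-square without continuity correction against the Mantel-Haenszel test, both at |z| > 1.96, with 100,000 trials per scenario:

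| Control risks by stratum | Type I error, unstratified | Power, unstratified | Power, stratified | Change |
|---|---|---|---|---|
| 20/20/20% | 5.1% | 78.5% | 78.3% | −0.2 |
| 12/20/34% | 4.4% | 78.7% | 79.4% | +0.7 |
| 6/20/45% | 3.3% | 80.1% | 82.9% | +2.8 |

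The stratified test holds its type I error at about 5% throughout. Simulated power with equal risks (78.5%) lies a little above the formula value because the formula is a normal approximation.

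**Standard error of the risk difference, 6/20/45%.** The odds ratio is about 0.178, and the taurolidine risks are about 1.1, 4.3 and 12.7%.

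- Unstratified: √[(0.2007 × 0.7993 + 0.05 × 0.95) / 68] = √(0.2079 / 68) = 0.0553.
- Stratified: mean within-stratum variance 0.1362 (control) + 0.0453 (taurolidine) = 0.1815; √(0.1815 / 68) = 0.0517.
- Ratio: 0.0517 / 0.0553 = 0.93, so the stratified standard error is about 7% smaller.

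**Sensitivity to stratum sizes.** With three equal strata, about 135 patients and 20% versus 5% overall:

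| Control risks | Type I error, unstratified | Power, unstratified vs stratified |
|---|---|---|
| 20/20/20% | 5.0% | 77.5 vs 77.3% |
| 15/20/25% | 4.5% | 77.5 vs 77.5% |
| 10/20/30% | 4.5% | 77.4 vs 78.1% |
| 5/20/35% | 3.9% | 77.7 vs 79.8% |
| 5/10/45% | 2.6% | 78.9 vs 82.9% |

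The pattern is the same: no gain when the strata are alike, under one point for moderate differences, and about 4 points in the most extreme set.

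**The case against.** **The article condenses a fuller protocol, and the analysis plan is not shown.** The primary-endpoint sentence names no test, the chi-square appears in a general list, and nothing says that the tests must be unstratified. This stands in part: the analysis plan may already stratify. But the article does name its tests, assigns the strata a role, and makes that role exploratory. Followed as written, it leads to a comparison that ignores the randomisation lists.

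**Adjusted models are planned.** Under Data collection, underlying disease and transplant type are recorded, so either model could include the stratum. But stepwise selection may drop it, and the multivariate analysis is described as a check on confounding with no covariates named.

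**The stratifier may not be prognostic.** This stands. The article gives no reason for its choice and no rates by stratum. With equal risks nothing is lost, and the stratified test costs about 0.2 points.

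**A reader might infer that the chi-square gives away part of the planned power.** The figures do not support this. With the pooled rates held at 20% and 5%, unstratified power is 78.5, 78.7 and 80.1%: it does not fall as the strata diverge. A lower figure appears if the odds ratio is instead fixed at 0.21: at 6/20/45% power is then 73.4% unstratified and 77.1% stratified. But the pooled taurolidine risk has then risen to 5.8% and the difference has shrunk from 15.0 to 14.3 points, so the fall from the equal-risk level reflects a smaller effect as well as the choice of test.

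**Conclusion.** The point holds as a conditional one. The design is stratified, the named tests are not, and no planned model secures the stratum. If the strata differ in colonisation risk, the chi-square and log-rank tests are conservative. For the chi-square, type I error falls to 4.4% or 3.3% in the two unequal scenarios, and the stratified standard error is up to about 7% smaller. At the planned 20% versus 5%, stratifying changes power by −0.2 to +2.8 points with strata of 60/42/34, and by up to about 4 points in the most extreme equal-strata scenario.

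These sizes rest on assumed stratum sizes and risks, a common odds ratio and a two-sided 5% level. The log-rank test was not simulated; only the direction is claimed for it.

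A reader might also infer a threat to validity. There is none: the crude comparison remains a valid one of the two arms, and its error rate is at or below nominal apart from simulation noise. Nor does this point explain the sample-size shortfall, which is a separate matter.

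**What to change.** In Statistical analysis, make the primary comparison a Cochran-Mantel-Haenszel test by randomisation stratum, or a logistic model with the stratum forced in rather than offered to stepwise selection. Report a stratified effect estimate with a 95% confidence interval. Use a stratified log-rank test for colonisation-free time. The unstratified chi-square and log-rank tests may stay as sensitivity analyses.

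Define the stratum as the list from which the patient was actually allocated, not as a group rebuilt from the recorded diagnosis. The inclusion criteria admit lymphoma, but no stratum is named for lymphoma without transplantation, so the two could differ.

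The cost is a sentence or two of wording, settled before unblinding. No new data are needed, since the pharmacy holds the lists.
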